#### 2.3.2. Secondary Outcome

The secondary outcome measure will be the difference in the mean scores between groups on the Generalized Anxiety Disorder Screener (GAD-7) at the same time points described above.

Anxiety symptoms will be assessed using the GAD-7, which is a self-administered instrument based on the criteria of the Diagnostic and Statistical Manual of Mental Disorders [47]. The total score ranges from 0 to 21, with the highest scores being the most severe [51]. The GAD-7 has been validated for use in Spanish-speaking pregnant women [52].

### 2.4. Inclusion and Exclusion Criteria

Inclusion criteria include being pregnant (participants can join the study at any time during their pregnancy), being over 18 years of age, understanding and speaking Spanish fluently, having a smartphone and the basic skills to operate it, and giving consent to participate in the study. The exclusion criteria for the study are not being pregnant, not understanding or speaking Spanish fluently and not having a smartphone or the basic skills to use it.

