## Abstract

Depression is the most common psychological disorder during the perinatal period, and its negative effects extend to mothers, babies, their family and society. Scientific evidence points to the urgency of designing preventive interventions and concludes that the gestational period is the most appropriate time to implement these interventions. However, many pregnant women do not seek professional help due to a lack of knowledge about the importance of mental health, its impact, and the available intervention options, as well as a lack of time and financial resources. E-health interventions can be an efficient, cost-effective, and accessible resource for preventing postpartum depression that can circumvent the barriers that pregnant women face. This randomized clinical trial will examine the efficacy of Healthy Moms and Babies, an app aimed at preventing postpartum depressive symptomatology. The second objective of this study is to analyze the effectiveness of the tool in preventing anxious symptomatology. The primary outcome measure is the difference in the mean score between the intervention and control groups on the Patient Health Questionnaire-9 (PHQ-9) at the end of the intervention and at 3 and 6 months postpartum. The secondary outcome will be determined by using the Generalized Anxiety Disorder Screener (GAD-7) at the same time points. The research findings can be used to determine pregnant women’s use of the e-health application for the prevention of postpartum depression, whether the Healthy Moms and Babies intervention app is an effective and useful resource, and what modifications will need to be made to the tool in future updates.

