### 2.2. Recruitment of Women

#### 2.2.1. Identification and Recruitment in the Obstetrics and Gynecology Department

The obstetricians and midwives who collaborate in the research will invite pregnant women who are undergoing obstetric follow-up at the Hospital Clínico San Carlos in Madrid to participate in the study. Interested individuals will be given a leaflet explaining the research with a QR code that they can scan with their smartphone to visit the initial web form that collects contact and socio-demographic data (age, gestational week, place of origin and residence, reference hospital, completed studies, employment status, marital status, and number of pregnancies, cesarean sections and/or previous abortions).

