### 2.5. Randomization

When participants access the Healthy Moms and Babies application for the first time, they will complete the baseline assessment including the PHQ-9 and GAD-7. Only participants who score between 5 and 19 on the PHQ-9 will be included and randomized into the treatment and control groups.

Based on the PHQ-9 score, called the $value, the Plesk software will distribute participants according to their level of symptomatology. Participants scoring <5 on the PHQ-9 have minimal depressive symptoms and therefore they will be excluded from the study and no further evaluation will be performed, but they will be offered access to the pregnancy information content. Participants scoring >19 on the PHQ-9 are considered to have severe symptomatology and will also be excluded from the study. In this case, these participants will be blocked from accessing the Healthy Moms and Babies application because it was not designed to address severe depressive symptomatology. Women will receive an alert message telling them to share their distress with someone close to them and to see a specialist for appropriate psychological care. Eligible patients (PHQ-9 score between 5 and 19) will be randomly assigned to the intervention and control groups according to the standard PHP function (mt_rand()) automatically generated by a computer. Women in the intervention group will have access to the psychological content modules and the general pregnancy information on the Healthy Moms and Babies app; women in the control group will only be able to access the informational content.

An independent researcher will program the mathematical algorithm that performs the randomization. Subsequently, simple blinding will be used, and participants will not be informed of the group to which they are assigned. The allocation will be known to the study team after it is performed automatically.

Outcome measures will be assessed at baseline, immediately after the intervention, and three and six months after the delivery date. At follow-up, questionnaires will be sent at the appropriate time by email and will be completed by the women via a web form.

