### 3.3. Overview of the Intervention

The psychological intervention was comprised of eleven modules with a similar structure: an introductory video, psychoeducational content, a practical exercise, general guidelines, and motivational messages. Considering that a new module was released every 4 days, the average duration of the intervention was six weeks. The components of the intervention are described in the following paragraphs and Table 1.

*Module 1. You are a mum:* welcomes, collects and validates all the emotions and sensations that a pregnant woman may experience, inviting her to make use of the app to live consciously during her pregnancy. The practical activity allows the participant to reflect on her emotions related to her pregnancy.

*Module 2. Psychoeducation:* validates any emotions related to pregnancy and motherhood, reducing guilt, and encouraging responsible action. It provides some facts and information about the baby blues, perinatal depression, and its consequences. The practical activity consists of pointing out the depressive symptoms with which the woman identifies and naming the situations in which she does so.

*Module 3. Feel better:* presents the story of Violeta and María, two women who encounter the same day, but with very different experiences. It addresses the individual responsibility of making choices to increase the feeling of well-being. The practical activity invites the participant to create positive loops of activities, thoughts, and emotions to help her through difficult moments.

*Module 4.**Thoughts:* proposes that the participant listens to her thoughts and identifies the emotions she feels with each thought, inviting her to question them, release them or reformulate them when they generate discomfort and do not conform to reality. In the practical portion, the app challenges the woman to transform her most negative and harmful thoughts into healthier ones.

*Module 5.**Enjoy the day:* addresses the importance of planning and prioritizing pleasant activities each day, highlighting their potential benefits for emotional health. It proposes that the participant reflects on five pleasant activities that can be done in their daily life and offers guidelines for time management and how to practice these guidelines daily.

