*Module 6.* Relax: relaxation is presented as a deactivation technique in stressful situations. The app offers women five relaxation audio clips and invites the women to practice them during pregnancy and after childbirth with their baby.

*Module 7.**Your body:* this module is the only one that does not propose a practical or reflective activity, and its content is basically informational. It provides information on the most common bodily and physiological changes during pregnancy.

*Module 8.**Find a solution*: differentiate between proactive and reactive tasks or emotion-focused coping strategies. The app proposes that the participant reflects on the aspects of her life that she wants to improve and invites her to look for alternative coping techniques to those she has used thus far.

*Module 9.**Social support*: highlights the importance of social support and differentiates between the different types. It also offers guidelines for assertive communication in the active search for support. This module suggests that the participant writes down a list of people who can provide support and suggests that she reflects on her support needs during pregnancy and the postpartum period.

*Module 10.**Goodbye myths*: uncovers the preconceived misconceptions about motherhood that can lead to frustration and suffering.

*Module 11.**Your baby*: addresses the participant’s expectations of what her baby will be like. It also offers some general guidelines for developing a secure attachment bond and some specific tips for handling very demanding babies.

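### Entry is open throughout pregnancy but the course takes at least 40 days to unlock: women joining after about week 34 cannot complete it before birth, which blurs the comparison without biasing it

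*Protocol article*

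**What the plan says.** Section 2.4 sets the entry window: "participants can join the study at any time during their pregnancy". No exclusion adds a latest gestational week: "The exclusion criteria for the study are not being pregnant, not understanding or speaking Spanish fluently and not having a smartphone" (or the skills to use one).

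Section 3.3 describes the course: "The psychological intervention was comprised of eleven modules with a similar structure". On timing it says: "Considering that a new module was released every 4 days, the average duration of the intervention was six weeks".

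The Abstract says of the scientific evidence that it "concludes that the gestational period is the most appropriate time to implement these interventions". The objectives (end of section 1, and section 3.2) are to prevent depressive and, secondarily, anxious symptoms after birth.

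Under section 2.3.1 the primary outcome includes the PHQ-9 at the end of the modules, or six weeks after starting in the control group, and again 3 and 6 months after delivery. Section 2.1 ties the follow-ups to the due date instead.

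Randomisation follows a baseline assessment at first login: "When participants access the Healthy Moms and Babies application for the first time, they will complete the baseline assessment including the PHQ-9 and GAD-7". Section 2.5 gives a simple random draw with no stratification. The web form in section 2.2.1 already records "age, gestational week, place of origin and residence" and other characteristics. Section 2.9 describes the primary analysis as a comparison of mean PHQ-9 scores and does not mention gestational week there.

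**The concern.** The course is presented as something delivered in pregnancy to prevent symptoms after birth. An entry window that runs to term does not leave every woman time for a six-week schedule. Three things follow for late entrants:

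- Part of the course falls after birth, so the arm contrast is a partly antenatal, partly postpartum course against information.
- The end-of-course score is taken after delivery, while an early entrant's is taken in mid-pregnancy. The PHQ-9 asks about sleep, fatigue and appetite, which birth itself can plausibly change.
- The 3- and 6-month scores follow soon after the course for late entrants and long after it for early ones.

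At stake is how the result is read. An average over these groups is harder to interpret as the effect of an antenatal course, and it may be smaller than that effect.

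**Working it through.** **Inputs from the article.** Eleven modules, one every 4 days, about six weeks (3.3); control post score at six weeks (2.3.1); follow-up at 3 and 6 months (2.1, 2.3.1, 2.5).

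**Assumed.** Birth at week 40, coinciding with the due date; module 1 on day 0; 3 months = 91 days and 6 months = 182 days. The article gives no distribution of gestational age at entry.

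**1. The plan's six weeks.** Module k unlocks on day 4(k − 1). Module 11 unlocks on day 4 × 10 = 40, or 40/7 = 5.7 weeks. Counting the last module's own interval, 4 × 11 = 44 days, or 6.3 weeks. Both round to the stated six weeks, so that figure reproduces.

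**2. Latest entry for antenatal completion.** 40 − 5.7 = 34.3 weeks, or 40 − 6.3 = 33.7 weeks: about week 34. With birth at week 37 it would be 31.3 or 30.7.

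**3. What each entry week gives.** With D = 7 × (40 − entry week) days to birth:
- modules unlocked before birth = min(11, floor(D/4) + 1)
- gap from last unlock to 3 months = (D + 91 − 40)/7, with 182 in place of 91 for 6 months
- control post score relative to birth = (42 − D)/7

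| Entry week | Modules unlocked before birth | Last unlock to 3 months (weeks) | To 6 months (weeks) | Control post score |
|---|---|---|---|---|
| 8 | 11 | 39.3 | 52.3 | 26 weeks before birth |
| 20 | 11 | 27.3 | 40.3 | 14 weeks before |
| 34 | 11 | 13.3 | 26.3 | at birth |
| 36 | 8 | 11.3 | 24.3 | 2 weeks after |
| 38 | 4 | 9.3 | 22.3 | 4 weeks after |

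**4. Share of late entrants, if entry is uniform up to week 40 (assumed).** From week 6: 5.7/34 = 17%. From week 12: 5.7/28 = 20%. From week 20: 5.7/20 = 29%.

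**5. Dilution, if benefit is proportional to modules unlocked before birth (assumed).** For late entrants spread evenly over the last 40 days, the mean number unlocked is (1 + 2 + … + 10)/10 = 5.5, half of 11. The average effect then falls by 0.5 × 17% = 8% up to 0.5 × 29% = 14%. The sample size for the same power rises by 1/(1 − 0.084)² = 1.19 up to 1/(1 − 0.143)² = 1.36. Section 2.8 gives no effect size, standard deviation or power, so this cannot be turned into a loss of power for this trial.

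**6. Would a cap at week 34 help precision?** Suppose a share f enters late with half the effect. The squared signal-to-noise ratio is proportional to (1 − f/2)² if they are kept and to 1 − f if they are excluded and not replaced. For f = 0.168 this is 0.839 against 0.832; for f = 0.286, 0.735 against 0.714. A cap gains nothing. If late entrants had no benefit, keeping them gives (1 − f)² = 0.692 against 0.832, and a cap would help.

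**The case against.** The best defence is that open entry is a reasonable pragmatic choice. Much of it stands.

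- **Late entrants do receive part of the course**: 8 of 11 modules before birth at week 36, 4 at week 38. Nothing says that access ends at delivery. Even a week-40 entrant could have everything unlocked about 5.7 weeks after birth, before the 3-month score.
- **The objectives do not require completion before birth.** The Introduction also accepts prevention in the first weeks after childbirth.
- **Later content is not purely antenatal.** Module 11 "addresses the participant’s expectations of what her baby will be like", but it also covers attachment and demanding babies. Modules 6 and 9 look to the period after birth as well. Module 7 is about pregnancy but mainly informational.
- **Gestational week is not ignored.** Section 2.2.1 lists it with the sociodemographic data, and section 2.9 will relate symptom severity to those characteristics and examine app use. That is descriptive, however, and does not bring entry timing into the arm comparison.
- **A covariate may already sit in an analysis plan that is not shown.** Its absence from the article is no fault. The entry rule and the unstratified draw, by contrast, are stated.

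A reader might go further and infer that late entrants cannot receive the course at all, that a null result would be uninterpretable, or that women could be randomised after delivery. The documents support none of these. The first fails on the module counts and the second on the planned data on app use. On the third, not being pregnant is an exclusion, and a condensed article that does not mention a second check at login does not show that there is none.

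**Conclusion.** The point holds as a matter of interpretation and efficiency. The stated entry window and course schedule do not fit together for entry after about week 34 (birth assumed at week 40). The end-of-course primary score mixes antenatal and postpartum measurements, and the gap to the 3-month score varies from about 39 to about 9 weeks between entry at weeks 8 and 38.

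Variation in entry timing does not bias the randomised comparison, because it is balanced between arms in expectation. It adds variation and may dilute the effect of an antenatal course. The documents do not allow the amount to be fixed. About 8% to 14% follows from uniform entry and benefit proportional to modules unlocked before birth, both assumed, and it is less if modules opened after birth also help. A figure as high as 29% would need zero benefit even in a woman who unlocks ten of eleven modules before birth, which nothing in the article suggests.

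**What to change.** 1. **Use gestational week at randomisation.** Take the value on the web form, moved forward by the days to first login. Either stratify the app's random draw by it (section 2.5) or include it as a covariate in the PHQ-9 and GAD-7 comparisons (section 2.9). The covariate needs no new data, only wording. Stratifying needs a change to the randomisation code and helps only women not yet randomised.

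2. **Pre-specify the arm effect by entry timing**: whether the six-week course could be completed before the due date. Keep all randomised women in the primary analysis. This costs wording only.

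3. **Reconcile section 2.4 with section 3.3.** Either set a latest entry week that leaves room for the course, or state that open entry and postpartum completion are intended, and say how delivery during the course is handled. The first option loses some third-trimester recruits, may not improve precision (step 6 of the working), and changes the population if made during recruitment. It would also leave most of the spread in follow-up gaps: about 39 to 13 weeks for entry between weeks 8 and 34. The second costs a sentence or two. Items 1 and 2 are worth doing under either option.

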### 2.5. Randomization

When participants access the Healthy Moms and Babies application for the first time, they will complete the baseline assessment including the PHQ-9 and GAD-7. Only participants who score between 5 and 19 on the PHQ-9 will be included and randomized into the treatment and control groups.

Based on the PHQ-9 score, called the $value, the Plesk software will distribute participants according to their level of symptomatology. Participants scoring <5 on the PHQ-9 have minimal depressive symptoms and therefore they will be excluded from the study and no further evaluation will be performed, but they will be offered access to the pregnancy information content. Participants scoring >19 on the PHQ-9 are considered to have severe symptomatology and will also be excluded from the study. In this case, these participants will be blocked from accessing the Healthy Moms and Babies application because it was not designed to address severe depressive symptomatology. Women will receive an alert message telling them to share their distress with someone close to them and to see a specialist for appropriate psychological care. Eligible patients (PHQ-9 score between 5 and 19) will be randomly assigned to the intervention and control groups according to the standard PHP function (mt_rand()) automatically generated by a computer. Women in the intervention group will have access to the psychological content modules and the general pregnancy information on the Healthy Moms and Babies app; women in the control group will only be able to access the informational content.

An independent researcher will program the mathematical algorithm that performs the randomization. Subsequently, simple blinding will be used, and participants will not be informed of the group to which they are assigned. The allocation will be known to the study team after it is performed automatically.

Outcome measures will be assessed at baseline, immediately after the intervention, and three and six months after the delivery date. At follow-up, questionnaires will be sent at the appropriate time by email and will be completed by the women via a web form.

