#### 2.2.2. Mass Recruitment on Social Media

In parallel to recruitment at the hospital, announcements and ads will be published on the social networks, Twitter and LinkedIn, encouraging pregnant women from the general population to participate in the research study. Women will be provided with a direct link to the website of the Healthy Moms and Babies project (https://blogs.uned.es/mbc/, accessed on 26 November 2021), which, in turn, redirects them to the initial web form.

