### 2.3. Outcomes and the Allocation of Participants to Trial Groups

#### 2.3.1. Primary Outcome

The primary outcome measure will be the difference in the mean scores between the intervention and control groups on the Patient Health Questionnaire-9 (PHQ-9) at the end of the psychological modules of the Healthy Moms and Babies application (in the case of the control group, the post assessment will be done six weeks after starting the PPP for the first time) and at three and six months after the delivery date.

The PHQ-9 is a nine-item instrument that assesses the severity of depressive symptomatology according to the following criteria of the Diagnostic and Statistical Manual of Mental Disorders [47]: depressed mood, markedly diminished interest in usual activities, significant increase or loss of appetite/weight, insomnia/hypersomnia, psychomotor agitation/retardation, fatigue or loss of energy, feelings of worthlessness or guilt, difficulty with thinking, concentrating or making decisions, and recurrent thoughts of death or suicide. The items are rated on four-point Likert-type scales, ranging from 0 (never) to 3 (almost every day), with higher scores indicating high severity of depressive symptoms (range 0–27). A score of 10 is the cut-off point recommended in clinical practice for estimating the presence of depressive symptoms [48,49]. However, considering that our aim is to prevent depressive symptoms, we will include all pregnant women who obtain a score equal to or greater than 5. The PHQ-9 has been validated in Spanish-speaking samples and in Spanish pregnant women [50].

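### Baseline routing and its only stated alert use the PHQ-9 total alone, so a positive death/suicide answer can be classed as minimal symptoms with no alert stated

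*Protocol article*

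**What the plan says.** Section 2.5 (Randomization) names the routing variable and the tool: "Based on the PHQ-9 score, called the $value, the Plesk software will distribute participants according to their level of symptomatology". It then gives three branches.

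- **Below 5.** These women "have minimal depressive symptoms and therefore they will be excluded from the study and no further evaluation will be performed". They are offered the pregnancy information content, and section 3.6 (Usual Care) repeats this.
- **5 to 19.** Eligible and randomised.
- **Above 19.** "Participants scoring >19 on the PHQ-9 are considered to have severe symptomatology and will also be excluded from the study". They are blocked from the app, and for this group the text adds: "Women will receive an alert message telling them to share their distress with someone close to them and to see a specialist".

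The alert sentence follows directly on the blocking of the high scorers and belongs to that branch. No other branch has an alert stated.

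Section 2.3.1 (Primary Outcome) lists the content of the nine items, the last being "recurrent thoughts of death or suicide". Each item is scored 0 to 3, the top answer meaning almost daily, and the total runs from 0 to 27. The article states no rule for the answer to any single item.

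**The concern.** A total score can be low while one answer is alarming. The death/suicide item is the one answer in this questionnaire that may call for a response in its own right, yet the stated trigger for the alert does not look at it. If the software is built exactly as section 2.5 describes, a woman who reports such thoughts almost every day, and little else, is labelled minimal and shown information on breastfeeding, nutrition and physical activity.

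The baseline questionnaire is completed in the app, and no clinician is said to be present. Section 2.2.2 adds recruitment through social networks, "encouraging pregnant women from the general population to participate in the research study", so a woman need not be under the care of the collaborating obstetricians and midwives. What is at stake is participant safety. The estimate of the treatment effect is not.

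**Working it through.** **Inputs.** Nine items scored 0 to 3 and a total range of 0 to 27 (section 2.3.1); cut-offs below 5, 5 to 19 and above 19 (section 2.5). The stated range reproduces: 9 × 3 = 27. The article gives no other figure that bears on this point.

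**Set-up.** Let d be the death/suicide item (0 to 3) and S the sum of the other eight items (0 to 24). The total is T = d + S.

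- T below 5 requires S ≤ 4 − d.
- T from 5 to 19 requires 5 − d ≤ S ≤ 19 − d.
- T above 19 (20 or more) requires S ≥ 20 − d.

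**Points on the other eight items that lead to each branch**

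| d | Below 5 | Randomised (5–19) | Alert (above 19) | Mean per other item needed for the alert |
|---|---|---|---|---|
| 1 | 0–3 | 4–18 | 19–24 | 19/8 = 2.375 |
| 2 | 0–2 | 3–17 | 18–24 | 18/8 = 2.25 |
| 3 | 0–1 | 2–16 | 17–24 | 17/8 = 2.125 |

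The maximum answer therefore gives T = 3 + 0 = 3 or T = 3 + 1 = 4 in the lowest branch, and the alert is reached only if the other eight items average at least 2.125 out of 3.

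**How narrow is the below-5 case?** The other eight items have 4^8 = 65,536 answer patterns. The number with sum 0, 1, 2 and 3 is 1, 8, 36 and 120. Cumulatively:

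- S ≤ 1: 1 + 8 = 9
- S ≤ 2: 9 + 36 = 45
- S ≤ 3: 45 + 120 = 165

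Full enumeration gives:

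| d | Below 5 | 5–19 | Above 19 | Sum |
|---|---|---|---|---|
| 1 | 165 | 64,156 | 1,215 | 65,536 |
| 2 | 45 | 62,848 | 2,643 | 65,536 |
| 3 | 9 | 60,412 | 5,115 | 65,536 |

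These counts show what the rule permits. They are not probabilities, because answer patterns are not equally likely. The article gives no rate at which women endorse the item, so no number of affected women follows.

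**Do other provisions catch the answer?**

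- Section 3.4: reminder emails are triggered by lack of progress in the modules and offer help with using the tool.
- Section 3.5: a psychologist trained for crisis needs handles email contact, but no questionnaire answer is stated to start that contact.
- Section 3.6: usual care continues, but nothing says that the treating clinicians see the answer.

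None of these is linked to the item.

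**The case against.** The strongest reply is that section 2.5 describes eligibility and allocation, not safety handling. An article condenses, and a check on this item would normally sit in the full protocol. For totals of 5 to 19 this objection largely stands: the article is silent there and the full protocol may fill the gap. For the routing itself it is weaker. The section names the software, the variable, every cut-off, the consequence of each branch and the content of the alert, and it ties that alert to the total.

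Three stronger readings are tempting, and the documents do not support them.

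- A reader might infer that the plan forbids any response to a worrying answer below 5. Ruling out further evaluation most likely means only that excluded women get no later trial questionnaires.
- A reader might infer that the alert is deliberately withheld from women at 19 or below. The article states one trigger; it does not say that there is no other.
- A reader might infer that excluded women have no access to the crisis-trained psychologist. Section 3.5 speaks of participants, and section 2.5 uses the same word for women it excludes, so that restriction cannot be read into the text.

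It is also fair to say that the below-5 case with the maximum answer is a corner: all eight other items at 0, or exactly one at 1.

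**Conclusion.** The point holds in a limited form. As stated, routing and the only stated alert depend on the PHQ-9 total alone. A woman with a positive death/suicide answer, even the maximum, can total less than 5, be classed as having minimal symptoms and receive only pregnancy information. At totals of 5 to 19 no alert triggered by the item is stated, subject to what the full protocol contains.

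The arithmetic is certain and needs only the item scoring and the cut-offs. The judgement that this is a gap assumes that the software follows section 2.5 as written and that no item check exists elsewhere; for that reason confidence is medium. The number of women affected is unknown. The primary comparison is not affected. It should be fixed because following the stated trigger exactly gives a worse safety outcome than a nearly free alternative.

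**What to change.** Add one condition to the baseline routing software: a positive death/suicide item, at a threshold set by the clinicians, shows the existing alert message in every branch, whatever the total. Add a matching sentence to section 2.5. If the full protocol already has an item check, cite it there instead.

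**Cost.** One software condition and probably a minor amendment, since the study already has review-board approval (section 2.7) and recruitment is set for 2020 to 2022 (section 2.1). Among randomised women the alert could act as a small co-intervention on the PHQ-9, so alerts should be recorded by arm.

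**Options for the sponsor.** The software could also notify the crisis-trained psychologist. The means exist, because women complete "the initial web form that collects contact and socio-demographic data", but the workload depends on the threshold and on an endorsement rate that the documents do not give, so this cannot be called cheap. The same check on the post-intervention and follow-up PHQ-9 is a suggestion only; the follow-up forms are sent by email, and someone would have to review the responses in time.
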